The Military Extremity Trauma Amputation/Limb Salvage (METALS) study applied methods similar to those in the LEAP study to the Operation Enduring Freedom/Operation Iraqi Freedom/Operation New Dawn (OEF/OIF/OND) military population [11]. This retrospective cross-sectional study included 324 U.S. Service members who had sustained major lower limb trauma as a result of high-energy blast and ordnance-related mechanisms. Both unilateral and bilateral lower limb traumatic injuries were included. Clinical data were obtained from participants’ medical records and through telephone interviews. Patients in the limb salvage and amputation groups reported significant disability compared to normal populations and 38% screened positive for depressive symptoms with 34% not working or in school at the time of the interview. Of interest, amputees reported better scores on the SMFA compared to limb reconstruction patients as well as lower rates of post-traumatic stress disorder. Only 17 limb salvage patients (~10%) in the study underwent revascularization [11]. These findings are in contrast to LEAP which reported similar health status measures in amputees and limb salvage patients, suggesting that translation of findings from non-combat civilian settings to combat injury may not be generalizable.

The Late Amputation Study Team (LAST) was to determine the prevalence of late amputations in wounded Service members from OEF/OIF/OND. While most amputations occurred in the acute setting, 15% of Service members sustaining lower extremity injuries had late amputations, defined as greater than 12 weeks after injury, range 12 weeks to 5.5 years [12]. A subset of these patients with type III open diaphyseal tibia fractures managed with late amputation were shown to have an increased incidence of infection [13].

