Our fourth aim is to describe long-term patient-reported outcomes in Veterans with traumatic vascular limb injuries controlling for potential confounders such as complexity of the combat injury (i.e., involvement of neurological and musculoskeletal components), traumatic brain injury, and comorbid mental and physical health conditions. Improvements in battlefield care, such as the use of temporary vascular shunts, transfusion methods, *etc.*, have evolved at a very rapid pace, but there is a need to understand the long-term outcomes of these treatments to inform clinical decision making and thus fully optimize trauma systems fielded in-theater. Findings from VAVIS will provide insight for military trauma, vascular and orthopedic surgeons to know which types of injuries can be repaired with adequate functional outcome to justify the initial surgical decision. It can be a particularly traumatic and demoralizing experience for a patient to undergo multiple procedures to attempt limb salvage only to lose the limb later due to ischemia, infection, extensive musculoskeletal injury or pain. A better understanding of outcomes will identify which patients may benefit from initial amputation versus attempts at vascular repair.

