### Study sample

Our denominator includes all individuals verified as having undergone initial in-theatre limb salvage (IILS) during the GWOT VI study. Inclusion criteria for IILS included: 1) received a vascular repair on the affected limb(s) and 2) transferred to the post-anesthesia unit and to the ICU after surgery. Individuals with amputations performed as the first, in-theatre operation are excluded.

To date, DoD chart abstractions using the Department of Defense Trauma Registry (DoDTR) have identified 1,363 individuals with confirmed extremity vascular injury and initial limb salvage; approximately 1,266 of these have separated from active service (Figure 2). Based on VA enrollment data, approximately 59% of OEF/OIF/OND Veterans discharged from the military have received VA health care [39], we expect approximately 700 individuals in the VA denominator. Database and chart abstraction components will include all those who received VA care (estimated N = 700). Additional analyses will be conducted for those who do not receive VA care within limits of available data.

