### Analytic plan

To address the first aim, we will compare injury, demographic and geospatial characteristics of patients IILS and identify late vascular surgery related limb complications and health care utilization in Veterans receiving VA vs. non-VA care using merged VA + VA-Medicare and DoD study data. We will identify vascular procedures performed, limb salvage survival time, and indicators of persistent morbidity over time (*e.g*., frequent/emergency care for vascular-related conditions, venous stasis disease, prosthetic use, long-term opioid therapy [VA patients only]). We will calculate descriptive statistics for all IILS patients’ demographic characteristics, long-term clinical outcomes (surgery related limb complications, time to amputation, persistent morbidity), and healthcare utilization (note that long-term use of opioid therapy will be assessed only among VA patients). We will also compare these descriptive statistics between those who received VA vs. non-VA care using chi-square tests for categorical variables and t-tests for continuous variables (with appropriate Box-Cox power transformation if necessary).

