To address the second aim, characterize the preventive services received by individuals with vascular repair and related outcomes, we will first compute the proportion of patients who receive antiplatelet agents, statins, annual duplex ultrasound, and vascular specialty care (and categories described above), and the percent patency each year for individuals without amputation. We will then examine the relationship between percent patency and preventive care using random effects analyses that models the vascular repair patency as a linear function of the indicator of receiving antiplatelet agents, statins, duplex ultrasound [51, 52], and other covariates/confounders (e.g., number of limbs affected, any initial, early or late amputations, mental health comorbidity, TBI diagnosis, and pre-existing chronic disease states such as atherosclerosis, diabetes, peptic ulcer disease), where the random effect is used to adjust for the within facility correlation, and the inverse of the propensity score for receiving antiplatelet agents/statins/yearly duplex ultrasound is adjusted for as weights. The adjustment of the propensity score for receiving antiplatelet agents/statins/yearly duplex ultrasound will minimize the estimation biases due to confounding by indication. We will also create different cut points (e.g. 75%, 50% patent), and use a binary outcome model. If Vascular Preventive Care processes are associated with positive patient outcomes, there will be support for these care processes as best practices.

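### The Aim 2 patency model conditions on late amputation, which can follow both preventive care and loss of patency, and its two amputation rules do not fit together

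*Protocol article*

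**What the plan says.** All places are in the Protocol article.

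- **Analytic plan, second aim, descriptive step.** The plan first computes shares receiving preventive care and "the percent patency each year for individuals without amputation".
- **Analytic plan, second aim, model.** It continues: "We will then examine the relationship between percent patency and preventive care using random effects analyses". The covariates/confounders named for that model include "number of limbs affected, any initial, early or late amputations, mental health comorbidity, TBI diagnosis". Nothing limits the amputations to those before the exposure, or to another limb. In the same list, the chronic diseases are limited to pre-existing ones. Inverse-propensity weights are added against confounding by indication.
- **Analytic plan, first aim.** Limb loss is an outcome here: the plan will identify "limb salvage survival time, and indicators of persistent morbidity over time" and describe "long-term clinical outcomes (surgery related limb complications, time to amputation, persistent morbidity".
- **Study sample.** "Individuals with amputations performed as the first, in-theatre operation are excluded". This leaves little for the word *initial* in the covariate list to refer to, except perhaps another limb.

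**The concern.** A covariate should be fixed before the exposure. Late amputation need not be. The background section on earlier orthopaedic and vascular studies reports that "15% of Service members sustaining lower extremity injuries had late amputations, defined as greater than 12 weeks after injury", and the Aims section describes patients who undergo attempts at salvage "only to lose the limb later due to ischemia, infection, extensive musculoskeletal injury or pain". Ischemia is thus one recognised route from a failed repair to a lost limb, and preventive care is studied because it may keep repairs open. Late amputation can therefore lie downstream of both the exposure and the outcome.

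Restricting to non-amputees removes some failed repairs from the denominator, and removes more of them from the group with more failures. Adjusting for late amputation absorbs part of the same difference. Weights that balance reasons for receiving care do not undo either step.

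At stake is the use made of the result. The plan says that an association would support these care processes as best practices, in a cohort described as being at risk of late amputation.

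**Working it through.** **1. The two rules side by side.** The modelling sentence uses the same percent patency as the descriptive step but does not repeat the restriction. If the restriction carries over, the amputation covariate is constant and drops out. If it does not, amputees stay in and late amputation is adjusted for. Only one mechanism can act on a given patient set, but each conditions on late amputation.

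**2. The plan's own power figure.** Inputs: N of about 700 (Study sample); 44.7% exposed, mean patency 50% to 60%, effect of 12%, power at least 0.84 (Analytic plan). The significance level is not stated; two-sided 0.05 is assumed, and 12% is read as absolute points.

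- Group sizes: 700 × 0.553 = 387 unexposed, 700 × 0.447 = 313 exposed.
- Take 50% versus 62% patent. The overall mean is 0.553 × 0.50 + 0.447 × 0.62 = 55.4%, within the stated range.
- Standard error under no difference: √[0.554 × 0.446 × (1/387 + 1/313)] = 0.0378. Under the difference: √[0.25/387 + 0.2356/313] = 0.0374.
- Power = Φ[(0.12 − 1.96 × 0.0378)/0.0374] = Φ(1.23) = 0.89.

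Other unexposed patency values from 44% to 60% give 0.886 to 0.916, consistent with the stated bound. A relative 12% would give only 0.35 to 0.50, so the absolute reading is the intended one.

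**3. Effect of conditioning on late amputation.** Let p be true patency, a₁ the late-amputation risk after a failed repair and a₀ the risk with a patent repair. These risks are assumptions. In all but the last row they are set so that 15% of the unexposed are amputated.

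- Restricted patency = p(1 − a₀) / [p(1 − a₀) + (1 − p)(1 − a₁)].
- The adjusted difference is the average of the differences among amputees and non-amputees, each weighted by m₀m₁/(m₀ + m₁), where m₀ and m₁ are the shares of unexposed and exposed patients in that stratum. Amputees are assumed to enter with their patency status before amputation.

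Worked case, a₁ = 30%, a₀ = 0:

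- Unexposed 0.50/(0.50 + 0.50 × 0.70) = 58.8%. Exposed 0.62/(0.62 + 0.38 × 0.70) = 70.0%. Difference 11.2 points; patency is overstated by about 8 to 9 points in both groups.
- Adjusted: weights are 0.2149 for non-amputees and 0.0316 for amputees. All amputees had failed repairs, so their difference is 0. The result is 0.2149 × 11.15/0.2465 = 9.7 points.

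| a₁ / a₀ | Amputated, unexposed / exposed | Restricted patency, unexposed / exposed | Restricted difference | Adjusted difference | Power, restricted |
|---|---|---|---|---|---|
| 15% / 15% | 15.0% / 15.0% | 50.0% / 62.0% | 12.0 | 12.0 | 0.836 |
| 20% / 10% | 15.0% / 13.8% | 52.9% / 64.7% | 11.8 | 11.8 | 0.832 |
| 25% / 5% | 15.0% / 12.6% | 55.9% / 67.4% | 11.5 | 11.0 | 0.825 |
| 30% / 0% | 15.0% / 11.4% | 58.8% / 70.0% | 11.2 | 9.7 | 0.816 |
| 50% / 0% (extreme) | 25.0% / 19.0% | 66.7% / 76.5% | 9.9 | 7.8 | 0.721 |

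In the first row there is no bias, and power falls from 0.89 to 0.836 through the smaller sample alone. In the next three rows most of the drop also comes from lost patients.

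**4. Check with a severity factor.** A simulation with an unmeasured severity factor affecting both patency and amputation, a true effect of 12 points and overall amputation of 16% to 30% gave 10.9 to 11.4 points restricted and 10.7 to 11.0 adjusted. With a true effect of zero it showed no bias. In both the table and the simulation, care affects amputation only through patency.

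**The case against.** The case on the other side is substantial, and much of it stands.

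- **The restriction is written only in the descriptive step.** An amputation covariate suggests that amputees stay in the model. A reader might infer that the analysis both drops amputees and adjusts for amputation, so that two biases add up. The text does not support that; it leaves open which rule applies.
- **Some amputations may precede the exposure.** Charts are abstracted from VA entry, which follows acute care and rehabilitation. An early or late amputation before preventive care begins is a legitimate baseline covariate, and removing all such terms would be wrong.
- **The phrase may be meant as an injury-burden marker.** It stands next to the number of limbs affected. This reading is possible but not stated.
- **Amputation is not the same as failed repair.** The Aims section also names infection, musculoskeletal injury and pain.
- **The timing of care relative to the patency reading is not described.** A reader might infer that care started because a repair was failing is counted as preventive. That rests on the silence of a condensed article, and the plan does plan weights for confounding by indication. It is not part of this point.

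What the objection does not remove is a stated covariate list that admits late amputation of the repaired limb after exposure, in an article that elsewhere treats time to amputation as an outcome.

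**Conclusion.** The point holds as an inconsistency and a badly fixed adjustment with a modest, assumption-dependent effect. Whichever rule applies, the Aim 2 model conditions on an event that can follow exposure and loss of patency. With about 15% late amputation, and failed repairs amputated more often than patent ones, a true 12 points becomes 11.2 to 11.8 restricted or 9.7 to 11.8 adjusted. The 15% comes from lower-extremity injuries in general, not from this vascular-repair cohort, and the split between failed and patent repairs is assumed. The bias vanishes if amputation is unrelated to patency. It also vanishes if the true effect is zero and care acts on amputation only through patency.

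A reader might infer that the analysis could hide a real benefit altogether. One can construct such a case, for example 10% versus 20% amputation with 60% patency among retained limbs in both groups, but equal patency among retained limbs builds in the zero. Nothing in the documents supports those rates. Nor do these scenarios produce false support for preventive care, since the distortion runs toward no effect.

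**What to change.** In the second-aim paragraph of the Analytic plan:

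1. Keep as covariates only amputations dated before the start of the preventive-care exposure, including those of another limb. Drop later amputation of the repaired limb from the list.
2. Keep patients who later lose the repaired limb in the analysis, with *repair patent and limb retained* as the outcome.
3. Report the components separately: patency, and amputation by cause where recorded.
4. Keep the analysis restricted to non-amputees as a sensitivity analysis.

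This needs plan wording and dated coding of data the study already intends to link and abstract; no new collection is required.

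The cost is that the outcome becomes a composite, which includes some amputations not caused by graft failure and answers a somewhat different question. Its expected difference is p₁(1 − a₀) − p₀(1 − a₀) = 0.12 × (1 − a₀): 12.0 points when only failed repairs are amputated, 10.8 at a₀ = 10% and 10.2 at a₀ = 15%. It can thus be smaller than the restricted contrast. Its advantage is that it compares all patients without selecting on a later event, and the separate components show where a difference arises.

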We will also conduct generalizability analysis using the inverse propensity probability weight technique. [53, 54] The goal is to examine whether the outcome model derived from the VA IILS patients (as described above) can be generalized to the non-VA IILS patients. We first derive model estimates for the VA cohort, then compute the propensity score for receiving non-VA care by modeling the log-odds of receiving non-VA care (vs. VA care) as a linear function of baseline covariates. The inverse propensity weighting is used to calibrate the outcome model derived from the VA IILS patients to the non-VA IILS patients. Finally we assess model generalizability by comparing model estimates between the VA vs. non-VA patients using the diagnostic method by Stuart et al. [55] This generalizability method does not require collecting outcomes for non-VA patients. However the credibility of this method relies on the “ignorability” assumption to hold true: conditioning on the covariates, the counterfactual outcomes of the non-VA patients (the patency outcomes should they receive VA care) would have been the same as the outcomes of the VA patients, and similarly, the counterfactual outcomes of the VA patients (the patency outcomes should they receive non-VA care) would have been the same as the outcomes of the non-VA patients.

Based on preliminary data from the TRACC study, we anticipate that the proportion of OEF/OIF/OND VA patients with ILLS will receive antiplatelet agents/statins/or yearly duplex ultrasound will be no greater than 44.7%. We also assume that the mean vascular repair patency falls between 50%-60%, and that the increased patency due to receiving antiplatelet agents/statins/or yearly duplex ultrasound is no less than 12% (conservatively). Under these conditions, the study will have ≥0.84 power to determine if Vascular Preventive Care processes are associated with positive patient outcomes.

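### The power of at least 0.84 for the second aim is not a guaranteed floor, because the exposed share is bounded only from above

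*Protocol article*

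**What the plan says.** The power paragraph for the second aim (protocol article, Analytic plan) sets three conditions and draws one conclusion.

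- **Exposed share:** the proportion of VA patients who "will receive antiplatelet agents/statins/or yearly duplex ultrasound will be no greater than 44.7" per cent. This is an upper limit, attributed to preliminary TRACC data. No lower limit is given.
- **Patency:** "We also assume that the mean vascular repair patency falls between 50%-60" per cent. The text does not say whether this is the mean in unexposed patients or overall.
- **Gain:** the increase in patency with preventive care "is no less than 12% (conservatively"). This is a lower limit.
- **Conclusion:** "Under these conditions, the study will have ≥0.84 power to determine if Vascular Preventive Care processes are associated with positive patient outcomes".

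The paragraph states neither the sample size nor alpha. The cohort size comes from the Study sample section: "we expect approximately 700 individuals in the VA denominator". The same section says that "Database and chart abstraction components will include all those who received VA care (estimated N = 700"). By contrast, the power paragraph for the third aim bounds its exposure share on both sides, at 10% and 50%.

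**The concern.** A statement that power is at least some value has to hold at the least favourable values its conditions allow. The gain is bounded on the right side for this purpose, because the smallest gain gives the lowest power. The exposed share is bounded on the wrong side. When the total number and the difference are fixed, power is greatest near an even split and declines as one group shrinks. An upper limit of 44.7% therefore fixes the best case and leaves the worst case open.

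The same section says that a positive association would support these care processes as best practices. If no association is found, a reader will take that result as coming from a study with at least 84% power. At shares the stated conditions allow, power could be nearer one half.

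**Working it through.** **Inputs from the document.** N = 700 (Study sample). Exposed share s at most 0.447, patency 0.50 to 0.60, and gain 0.12 (Analytic plan).

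**Assumptions.** Two-sided alpha of 0.05, since none is stated. The 12% is read as percentage points: read as a relative increase, power at 44.7% would be only 0.35 to 0.50, far from the plan's figure. The 50% to 60% is read as unexposed patency. All 700 are taken as analysable. This favours the plan, because patency is reported as "the percent patency each year for individuals without amputation" and the number removed by that restriction is not given.

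**Formula (unpooled variance).** With n1 = sN exposed, n0 = (1 − s)N unexposed and p1 = p0 + 0.12:

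SE = √[p0(1 − p0)/n0 + p1(1 − p1)/n1], power = Φ(0.12/SE − 1.96).

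The pooled version uses the pooled variance for the critical value and is slightly lower.

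**Step 1: the plan's own figure.** At s = 0.447, n1 = 313 and n0 = 387. For 0.50 against 0.62, SE = √(0.25/387 + 0.2356/313) = 0.0374, so power = Φ(3.21 − 1.96) = 0.89. For 0.60 against 0.72, power is 0.92. The exact value 0.84 is not reproduced at N = 700, but the inequality is true at this share.

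**Step 2: smaller shares that the conditions allow.** For example, at s = 0.20, n1 = 140 and n0 = 560. SE = √(0.25/560 + 0.2356/140) = 0.0461, and power = Φ(2.60 − 1.96) = 0.74.

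| Exposed share | p0 = 0.50, pooled / unpooled | p0 = 0.60, pooled / unpooled |
|---|---|---|
| 44.7% | 0.89 / 0.89 | 0.92 / 0.92 |
| 30% | 0.835 / 0.844 | 0.87 / 0.88 |
| 20% | 0.72 / 0.74 | 0.76 / 0.79 |
| 10% | 0.48 / 0.50 | 0.50 / 0.56 |

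Reading 50% to 60% as the overall mean changes little: 0.72 to 0.78 at 20% and 0.48 to 0.55 at 10%.

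**Step 3: where 0.84 is lost.** Solving for the share at which power equals 0.84 with N = 700 gives 29% (unpooled) or 31% (pooled) at p0 = 0.50, and 24% or 27% at p0 = 0.60.

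**Step 4: patency as a continuous outcome.** The lead model treats patency as a linear function of the covariates, so a per-patient percentage may be meant. The document gives no SD. With power = Φ(0.12/[SD·√(1/n0 + 1/n1)] − 1.96) and N = 700:

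| Assumed SD | 20% exposed | 10% exposed |
|---|---|---|
| 0.45 | 0.81 | 0.56 |
| 0.40 | 0.89 | 0.66 |
| 0.35 | 0.95 | 0.78 |

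An SD of 0.30 gives 0.89 at 10%. Even there, power falls to 0.64 at 5% exposed (n1 = 35, n0 = 665). A smaller SD moves the share at which 0.84 is lost but does not remove it.

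**The case against.** Several points on the other side have weight.

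- **0.84 is not a ceiling.** A reader might infer that, with the share capped at its best value, 0.84 is the most power the study can have. The document does not support this. At N = 700 and a 12-point gain, shares from about 31% to 44.7% give 0.84 or more under every formula used here. The gain is also only bounded below: 15 points at 20% exposed gives about 0.90. This stands, and the point is limited to the missing floor.
- **Low shares are not forecast.** Nothing in the document says that 10% or 20% is expected, and 44.7% may be the top of an estimate close to it. A reader might infer that any single process must have a low share, because 44.7% covers any of the three. The wording can equally be a limit on each. This stands as a caution on likelihood. It does not repair the claim, which is made for all shares up to the limit. The Background itself says that statin prescribing in this population is unknown and that no information exists on how far duplex surveillance is met.
- **Weighting and clustering.** A reader might infer that the figure ignores the propensity weights and the facility effect. The gap between 0.89 and 0.84 could equally mean that some allowance was made, and an article may leave that detail to the full protocol. No loss for weighting or clustering is counted here.
- **Outcome type.** A continuous outcome would have more power, as the working shows. That softens the figures at 20% but does not give a floor at every share allowed.
- **No design consequence.** The cohort is everyone who received VA care, so no recruitment target depends on the figure. This bears on the cost of the fix, not on whether the sentence is correct.

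**Conclusion.** The claim is wrong as written: power of at least 0.84 does not follow from the conditions attached to it. It holds at the 44.7% limit and for some distance below it, then fails once the exposed share is under roughly 24% to 31%, depending on patency and the variance formula. It is about 0.72 to 0.79 at 20% and 0.48 to 0.56 at 10%. These sizes rest on N of about 700, a 12-percentage-point gain, a two-sided 5% level and a binary patency outcome. The last two are assumptions, as is the percentage-point reading. The direction of the error depends only on holding the sample size and the difference fixed.

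**What to change.** Replace the statement with the power at the exposed share actually used in the calculation, naming the sample size and alpha. Add the smallest share for which 0.84 holds, or set a lower limit on the share as the third aim does, and show how power falls at smaller shares. If the original calculation used N of about 700, a two-sided 5% level and a binary outcome, the text could say that power for a 12-point gain is about 0.89 to 0.92 at 44.7% exposed, stays at 0.84 or above down to a share of roughly 24% to 31%, and is about 0.72 to 0.79 at 20% and 0.48 to 0.56 at 10%. If it used a different sample size, or a continuous outcome with a given SD, those inputs should be stated and the figures recomputed from them. The change is to text only and needs no extra patients. The cost is a less favourable stated power.
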